### Provisions for post-trial care {30}

All study participants will still receive standard care and extended follow-up after the study is ended, and they can claim reimbursement from the study insurance to compensate for trial-associated harm.

### Outcomes {12}

#### Primary outcome

The primary outcome is a recurrence rate of CSDH up to 6 months after surgery. Recurrence is defined as the occurrence of symptoms and signs attributable to an ipsilateral hematoma seen on a CT scan within 6 months of the original drainage procedure.

#### Secondary outcome

Secondary outcomes include functional outcome (modified Rankin Scale, mRS score [10] and Markwalder Grading Scale, MGS grade [11]) at baseline, and at 1, 3, and 6 months; quality of life (five-dimensional EuroQol, EQ-5D-5L [12]) at baseline, and at 1, 3, and 6 months; mortality at 6 months; and rate of complications and adverse events between groups within 6 months.

### Participant timeline {13}

Participants in the intervention and control groups will undergo six scheduled follow-up visits, respectively. The participant timeline is shown in Table 1.

**Table 1 Tab1:** Schedule of enrollment, interventions, and assessments

	**Enrolment**	**Surgery**	**After surgery**			
**Time point**	**Ad**	**IO**	**D1**	**1 mon**	**3 mon**	**6 mon**
**Enrollment**						
Eligibility screen	X					
Informed consent	X					
Randomization	X					
**Interventions**						
Exhaustive or fixed-time (48 h) drainage		X	X			
**Assessments**						
Demographics, medical history	X					
Laboratory data	X		X	X	X	X
Neurological examination	X		X	X	X	X
Computed tomography	X		X^#^	X	X	X
mRS	X			X	X	X
MGS	X			X	X	X
EQ-5D-5L	X			X	X	X
Complications		X	X	X	X	X
Mortality				X	X	X
Economic data						X
(S) AEs		X	X	X	X	X

*Ad* admission, D day, *EQ-5D-5L* EuroQoL 5-Dimension 5-Level questionnaire, *h* hours, *IO* intraoperative, *mon* months, *MGS* Markwalder Grading Scale, *mRS* modified Rankin scale, *(S) AE* (severe) adverse event

^#^Only in exhaustive drainage group

### Recruitment {15}

The ECHO trial will recruit in 19 hospitals in China, and there are two research members from the department of neurosurgery in each study site who will be in charge of the patient recruitment process.

### Assignment of interventions: allocation

#### Sequence generation {16a}

Eligible participants will be randomly assigned by a computerized random-number list generator used for randomization in a web-based, GCP-compliant electronic data capture (EDC) system, after written consent is obtained. Randomization is done separately in each center.

#### Concealment mechanism {16b}

Participants are randomized using the EDC system for collecting patients’ data in clinical trials. To ensure allocation concealment, the system will release the randomization code after the patient has been recruited into the trial. Participants who give consent to participate and who fulfill the inclusion criteria will be recruited by the neurosurgeons involved in the ECHO trial. The randomization will be firstly released after the signed consent form is uploaded to the system.

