### Methods: participants, interventions, and outcomes

#### Study setting {9}

This is a multicenter study that will be conducted from December 2020 to May 2023 at 19 hospitals in China. In the participating centers, all patients who are diagnosed with a CSDH are tested for eligibility for the ECHO study. After gaining informed consent, patients are randomized to either the treatment or the control group. Research is facilitated by a leader center to guarantee compliance with protocol, adherence to International Conference on Harmonization-Good Clinical Practice (ICH-GCP), and data safety.

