### Who will take informed consent? {26a}

Informed consent will be obtained from all participants in the study prior to surgery of the CSDH. Based on the inclusion and exclusion criteria, patients will be screened for study participation. A verbal explanation of the written consent will be provided by the attending neurosurgeon, and any questions regarding the rationale, design, risks, and potential benefits of the study will be answered. Each participant will have sufficient time to decide whether to participate in this study. If the patient is unable to give consent, consent will be sought from a close relative. Withdrawal from the study is possible at any time, in accordance with the latest version of the declaration of Helsinki 2013.

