### Interventions

#### Explanation for the choice of comparators {6b}

All participants will be treated with a one-burr-hole craniostomy with irrigation and a closed drainage system. In fixed-time drainage (control group), the drainage will be removed after 48 h postoperatively. In exhaustive drainage (treatment group), the drainage will be removed when postoperative hematoma volume is minimized with repeated urokinase injection into the hematoma cavity through a catheter based on a postoperative CT scan.

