### Postoperative drainage strategy

In the fixed-time drainage group, the drainage will be removed after 48 h postoperatively. In the exhaustive drainage group, if the CT scan on the first day after surgery (postoperative 24 ± 4 h) indicates no obvious hematoma left(hematoma shows no high density and has less than 3 mm of maximum width in axial CT scan images), the drainage catheter will be removed when drainage ceases. If subdural collections remain in the hematoma cavity (hematoma shows high density and has more than 3 mm of maximum width in axial CT scan images), the participant will be treated with 30,000U urokinase injection into the hematoma cavity through the catheter. The catheter will be closed and reopened in 2 h, and a CT scan will be performed when drainage ceases. If the CT scan shows residual hematoma eliminated, the catheter will be removed. However, if there is still a residual subdural collection, the above steps will be repeated. If the participant is subjected to urokinase injection for 3 times, the catheter will be removed when drainage ceases.

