### Strategies to improve adherence to interventions {11c}

Study treatment takes place after enrollment, and follow-up visits take place at 1, 3, and 6 months. At enrollment, participants will receive detailed instructions about burr-hole craniostomy and the corresponding postoperative drainage strategy. Moreover, the importance of adherence to the study protocol is emphasized.

During follow-up visits at 1, 3, and 6 months, treatment adherence is monitored by asking whether the participant experiences any side effects or AEs. Study participants can contact one of the researchers with any questions during the study period. The whole study process is continuously monitored by a blinded local researcher in each center who performs the follow-up outcome measurements.

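### The allocation is released before an operation that is the same in both arms, so the operating team can know the arm during surgery for no stated reason

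*Protocol article*

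**What the plan says.** **Timing of allocation.** Who will take informed consent? {26a} states: "Informed consent will be obtained from all participants in the study prior to surgery of the CSDH". Study setting {9} continues: "After gaining informed consent, patients are randomized to either the treatment or the control group". Concealment mechanism {16b} adds: "The randomization will be firstly released after the signed consent form is uploaded to the system". In Table 1 the row "Randomization" is marked in the admission column, ahead of the surgery column. Strategies to improve adherence to interventions {11c} says: "At enrollment, participants will receive detailed instructions about burr-hole craniostomy and the corresponding postoperative drainage strategy".

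**Where the arms part.** Explanation for the choice of comparators {6b} states: "All participants will be treated with a one-burr-hole craniostomy with irrigation and a closed drainage system". Under Postoperative drainage strategy the first arm-specific instruction begins: "In the exhaustive drainage group, if the CT scan on the first day after surgery (postoperative 24 ± 4 h) indicates no obvious hematoma". Control drains are removed after 48 h. Table 1 marks the day-1 CT as applying to the exhaustive group only.

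**Who is blinded.** Who will be blinded {17a} and Procedure for unblinding {17b} limit blinding to the follow-up investigators, the outcome assessors and the data analysts.

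**Analysis set.** Section {20c} specifies intention to treat and keeps every enrolled participant in the analysis.

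**The concern.** Nothing in the operation depends on the arm, so nobody in the operating room needs to know it. Releasing the code at consent makes it available to a team that is not blinded and whose work precedes the randomized contrast.

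This matters because of the protocol's own rationale. Background and rationale {6a} reports that postoperative hematoma volume predicts recurrence (Exp(B) 1.028, 95% CI 1.011–1.046), and how completely the hematoma is evacuated at surgery acts on that volume. If evacuation differed by arm, the comparison would mix surgical conduct with drainage strategy. A blinded assessor at 6 months would faithfully record a difference that arose in the operating room.

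The secondary issue is dilution. A patient randomized at admission whose operation is then cancelled or aborted never meets the contrast between drainage strategies, but is still counted in the assigned arm.

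**Working it through.** **1. Sequence of events as written**

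| Step | Timing | Arm-specific? | Source |
|---|---|---|---|
| Consent | before surgery | no | {26a} |
| Code released | once the consent form is uploaded | – | {9}, {16b}, Table 1 |
| Patient instructed on the drainage strategy | enrollment | appears so | {11c} |
| Burr hole, irrigation, catheter | surgery | no | {6b}, Operation |
| First CT-guided decision | 24 ± 4 h after surgery | yes, exhaustive arm | Postoperative drainage strategy, Table 1 |
| Drain removal | after 48 h | yes, control arm | Postoperative drainage strategy |

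The earliest arm-specific step is 24 − 4 = 20 h after surgery. The code could therefore be released at any time in a window of about 20 h after the operation without touching either strategy. No section gives a reason for releasing it earlier.

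**2. Discretion left in the operation**

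The Operation section fixes the burr-hole size and site, 1000 mL of irrigation, the catheter depth and direction, and the height of the collection bag. Left to judgment are when the irrigation fluid counts as clear, how the catheter is worked through the cavity, and when local anesthesia is not tolerated. The room for difference is limited but not nil. The documents offer nothing from which its effect on recurrence could be estimated, so no figure is given.

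**3. The plan's own sample size**

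Inputs from Sample size {14}: p1 = 0.10, p2 = 0.02, power 80%, alpha 5% (taken as two-sided), 1:1. Mean p̄ = 0.06. Pooled z-test without continuity correction:

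n = [1.960·√(2·0.06·0.94) + 0.842·√(0.10·0.90 + 0.02·0.98)]² / 0.08² = 137.2, rounded up to 138 per group, 276 in total. This matches the plan.

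Power = Φ[(|p1 − p2| − 1.960·√(2p̄(1 − p̄)/n)) / √((p1(1 − p1) + p2(1 − p2))/n)]. At n = 138: (0.08 − 1.960 × 0.02859)/0.02818 = 0.850, so power is 80.2%. At n = 152 it is 83.9%.

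**4. Dilution, by assumption**

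Let f be the share of randomized patients who never reach the drainage phase. The documents give no value for f.

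- *Case A:* these patients carry 10% risk in both arms. Then p1 = 0.10 and p2 = 0.02(1 − f) + 0.10f.
- *Case B:* these patients have no events. Then p1 = 0.10(1 − f) and p2 = 0.02(1 − f).

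| f | Power at 138, A | Power at 138, B |
|---|---|---|
| 0% | 80.2% | 80.2% |
| 1% | 79.2% | 79.8% |
| 2% | 78.1% | 79.4% |
| 5% | 74.7% | 78.0% |
| 10% | 68.8% | 75.6% |

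Worked line for f = 5%, Case A: p2 = 0.019 + 0.005 = 0.024; (0.076 − 1.960 × 0.02903)/0.02867 = 0.666, giving 74.7%. Case B: p1 = 0.095 and p2 = 0.019, giving 78.0%.

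If all 152 per group were evaluable, f = 5% gives 78.7% (A) or 81.9% (B), against 83.9% with no dilution. Each 1% of such patients costs at most about one percentage point of power.

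**The case against.** **The sequence is consistent and conventional.** Consent, randomization and surgery follow in that order throughout, and the trial is declared open-label with blinded endpoint assessment. That stands: the text contains no contradiction here. The point is that the choice costs something and nothing stated is gained by it.

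**The operation is standardized.** This is the strongest reply, and it largely stands. It narrows the route for bias but does not close it, because the judgments listed above remain.

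**The text does not say that the surgeon sees the code.** Correct. A reader might state as fact that the surgeon operates knowing the arm, but {16b} gives only the earliest release. The inference is well supported: trial neurosurgeons recruit, patients are instructed at enrollment, and no section withholds the code from the operating team. It is still an inference.

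**Two other readings go too far.** A reader might infer that allocation concealment fails. It does not, because the code comes only after consent and recruitment. A reader might also put a false-positive rate on the bias by supposing some recurrence difference due to surgery alone. The documents support no such difference, nor its sign: a surgeon who expects later drainage steps might evacuate less, and one who favors the strategy might evacuate more.

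**Dilution is probably small.** This also stands. The exclusion criteria already remove patients who do not need surgery or cannot tolerate it. Recurrence is counted from the original drainage procedure, so a patient never operated on could hardly have an event, which favors Case B.

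**Conclusion.** The point holds as a design weakness that could have been avoided. Release before surgery lets an unblinded team know the arm during a step that is common to both groups and that influences the protocol's own predictor of recurrence. The resulting performance bias has unknown size and direction, so it could weaken either a positive or a null result. The standardized operation makes a large effect less likely.

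Dilution is a secondary matter and is conditional on a rate the documents do not give. At an assumed 5%, the loss is about 2 to 5.5 percentage points of power at 138 per group (80.2% to 74.7–78.0%), and about 2 to 5 points at 152 per group (83.9% to 78.7–81.9%). The 10% enrollment allowance is meant for drop-out and loss to follow-up, not for this. The documents do not show that dilution will occur at any material rate.

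**What to change.** Keep consent before surgery. Set the electronic data capture system to release the allocation only after skin closure has been recorded and before the 24 ± 4 h CT. Align Study setting {9}, Sequence generation {16a} and Concealment mechanism {16b}, and move randomization in Table 1 from admission to after surgery. Reword {11c} so that patients are told at enrollment about both possible strategies and learn their own only after the operation.

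This removes arm knowledge from the operating room and the losses before and during surgery. Patients who lose the drain after release but before the CT would still dilute the comparison.

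**Cost.** One system entry after surgery, and consented patients whose operation is aborted are not randomized. Trial status says that recruitment began in December 2020, so the change needs an amendment under section {25} across 19 hospitals. It would apply to remaining patients only and leave a population randomized partly before and partly after surgery. If the timing is not changed, the protocol should at least justify the early release, and the report should give the number of randomized patients per arm who never reached the drainage phase.

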#### Implementation {16c}

An experienced sub-investigator, not involved in any other aspect of this study, will use the online EDC system to generate a computerized random-number list, which will allocate participants to either one of the two groups. Extended stratified block algorithms generate an unpredictable allocation sequence. Random assignment cannot be influenced by clinical investigators.

### Assignment of interventions: blinding

#### Who will be blinded {17a}

The investigators in charge of the postoperative follow-up evaluation will be blinded, along with the outcome assessors and data analysts.

#### Procedure for unblinding if needed {17b}

The design is open labeled with only the investigators for postoperative follow-up evaluation, the outcome assessors, and data analysts being blinded, so unblinding will not occur. Before the outcome assessment begins at every follow-up evaluation, the patients will be reminded not to reveal any information about their group allocation for decreasing the risk of unblinding. If details of group allocation can be detected by the investigator during follow-ups, another blinded researcher will replace to evaluate the outcome.

### Data collection and management

#### Plans for assessment and collection of outcomes {18a}

The outcome of interest will be collected by a group of blinded research members in charge of the follow-up evaluation and be recorded in the EDC system, which will only be accessible to the sub-investigators. At the completion of the 6-month follow-up data collection, we will perform a data quality audit. An investigator will sample every participant file and check for missing data.

#### Plans to promote participant retention and complete follow-up {18b}

Follow-up will be conducted on 1, 3, and 6 months after discharge by an experienced research member blinded to the study. All the participants will complete a 6-month follow-up. Follow-up data collection will be done in person during the patient follow-up visits. Any participants who do not complete the entire 6-month follow-up process due to deviation from intervention, discontinuation for personal reasons, or failure of contact, will not be replaced by other patients. Participants will be allowed to withdraw their consent or discontinue participation without any restriction, at any time throughout the study and further data associated with the trial will be collected.

### Data management {19}

All data collected will be stored in an online EDC system accessible only to investigators. Primary and secondary outcomes will be collected by a group of blinded research members in charge of the postoperative follow-up evaluation. At the completion of the 6-month follow-up data collection, a data quality audit will be performed.

### Confidentiality {27}

All personal information about the participants will be collected and stored in a secure EDC system, throughout the duration of the study, to guarantee confidentiality. All participants will be allocated by individual trial identification numbers. Only the lead investigator will have access to all the files corresponding to the personal data of the participants.

### Plans for collection, laboratory evaluation, and storage of biological specimens for genetic or molecular analysis in this trial/future use {33}

This trial does not involve collecting, laboratory evaluation, and storage of biological specimens for genetic or molecular analysis.

### Statistical methods

#### Statistical methods for primary and secondary outcomes {20a}

Statistical analyses will be performed using a statistical package (SPSS software 25.0). The Kolmogorov–Smirnov test will be used to assess the normality of variables. Data for normal distribution will be presented as mean ± standard error of mean. Variables for skewed distributions will be described as median and interquartile ranges. Categorical variables will be expressed as frequencies with percentages.

Comparisons between the groups will be carried out using an independent *t*-test to compare normally distributed data, the Mann–Whitney *U* test to skewed data, and *χ*^2^ test or Fisher’s exact test to compare categorical data such as safety analyses with the incidence of AEs. For numerical data collected at different time points throughout the course of 6 months, repeated measures analysis of variance will be performed between the two groups. The significance level will be set at *p* < 0.05.

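### A normality pre-test on the trial data chooses how numeric secondary outcomes are summarised and, for single-time comparisons, tested, and it is not reconciled with an unconditional repeated-measures ANOVA

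*Protocol article*

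**What the plan says.** Three statements in the protocol article's section on statistical methods for primary and secondary outcomes {20a} bear on this point.

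- The sorting rule: "The Kolmogorov–Smirnov test will be used to assess the normality of variables".
- Its consequences. For the summary: "Data for normal distribution will be presented as mean ± standard error of mean", but "Variables for skewed distributions will be described as median and interquartile ranges". For the between-group comparison, an independent t-test is used "to compare normally distributed data, the Mann–Whitney *U* test to skewed data".
- The rule for repeated data: "For numerical data collected at different time points throughout the course of 6 months, repeated measures analysis of variance will be performed". It depends on no normality result and names no alternative for skewed data.

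The Secondary outcome section lists mRS and MGS as functional outcomes "at baseline, and at 1, 3, and 6 months; quality of life" on the same schedule. The primary outcome is recurrence, which is binary and falls under the chi-square or Fisher rule.

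**The concern.** The first two statements let the outcome data decide whether a numeric variable is reported and compared through means or through ranks. These are different quantities, and the choice should rest on the scale and the question asked.

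The third statement then applies a mean-based model to repeated numeric data whatever the pre-test found. The section does not say whether the ANOVA replaces the t-test or Mann–Whitney comparison or is added to it. The Objectives {7} section frames the clinical benefit at 6 months, a single-time contrast to which the first rule would naturally apply. Both rules can therefore cover mRS, MGS and EQ-5D-5L, with no order of precedence.

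At stake is how the secondary results behind the claim of better clinical outcomes are expressed, and whether that was settled before the data were seen.

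**Working it through.** **1. The sample size at which the pre-test operates.** The plan gives no figure for the pre-test itself. Its evaluable size, 138 per group, comes from Sample size {14} and is reproduced with 10% versus 2% recurrence, two-sided 5%, 80% power and pooled variance:

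n = [1.960·√(2·0.06·0.94) + 0.842·√(0.10·0.90 + 0.02·0.98)]² / 0.08² = (0.658 + 0.279)² / 0.0064 ≈ 137.2, rounded up to 138.

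**2. Short ordinal scales.** The statistic is D = max |Fₙ(x) − Φ((x − x̄)/s)|. If a share p of patients has the same score, Fₙ jumps by p there and a continuous curve cannot follow, so D ≥ p/2. The approximate 5% limit without correction for estimated parameters is √(½·ln(2/0.05))/√138 = 1.358/11.75 = 0.116. With assumed largest category shares of 0.30 (mRS-like, baseline), 0.35 (mRS-like, follow-up) and 0.60 (MGS-like), D is at least 0.15, 0.175 and 0.30. In 2,000 simulated trials per scale, the test rejected in 100%, with and without the Lilliefors correction.

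**3. A moderately skewed score without a ceiling.** Assumptions: gamma shapes 20, 8 and 4 (skewness 2/√shape), 5% pre-test level, 2,000 trials each.

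| Skewness | 0.45 | 0.71 | 1.0 |
|---|---|---|---|
| Lilliefors rejects, one arm (138) | 20% | 47% | 78% |
| Uncorrected rejects, one arm | 0.5% | 3.5% | 19% |
| Lilliefors rejects, pooled (276) | 37% | 80% | 98% |
| Uncorrected rejects, pooled | 2% | 18% | 60% |
| The two versions disagree, pooled | 35% | 62% | 38% |

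A 0–100 score with mild left skew (−0.53, assumed) behaves alike: per arm, Lilliefors rejects in 43% and the uncorrected test in 2%.

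**4. A capped EQ-5D-like score (assumed).** Pooled, both versions reject in 100%. Per arm, Lilliefors rejects in 100% and the uncorrected test in 93%.

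**5. Error rates for a single-time comparison.** With no treatment effect, skewness 0.71 to 1.4, 138 per arm and 3,000 trials each, the pre-test followed by t or Mann–Whitney rejects in 4.6% to 5.7%. Either test alone gives 4.6% to 5.6%. The two tests reach different significance verdicts in 2% to 3%.

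**6. The rules side by side.** Suppose mRS is treated as numeric. By step 2 it is judged non-normal, so the summary is a median and the single-time test is Mann–Whitney. By the repeated-data rule the same variable goes to ANOVA on means. The text does not say which result is the treatment effect.

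**The case against.** The strongest reply is that the ANOVA sentence governs. All three scale-type outcomes are repeated, so their stated analysis is one model, and the pre-test settles only the descriptive summary. A reader might infer that every numeric outcome will be tested by a method that switches between visits. The documents do not support that, because per-visit t or Mann–Whitney tests are nowhere specified for repeated data. This part of the reply stands. What it leaves is the unstated precedence between the two rules and a median summary beside a test on means.

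Second, switching is largely theoretical for the named outcomes. For mRS and MGS the verdict is always the same, and for a capped EQ-5D score nearly always. This also stands, but a test with a foregone answer is no reason to keep it. The verdict is unstable only for a moderately skewed score without a ceiling. The documents do not say how the EQ-5D-5L score will be formed or distributed.

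Third, the percentages rest on assumed shapes and an inferred 5% level, and the per-arm figures also assume testing within arms. This is correct, so they show a range and do not predict this trial. One might also infer that a software setting alters the results. The article names only SPSS 25.0, and the comparison here is between two forms of the test.

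Fourth, an analysis plan that is not shown may fix the level, the unit of testing and the version. Their absence is not counted as a fault here. The data-driven rule, however, is stated in the protocol, and a plan that named one method per outcome would depart from it.

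**Conclusion.** The point holds as a minor one, confined to secondary outcomes. The protocol lets an uninformative pre-test choose the summary and any single-time test, and it sets beside this a mean-based ANOVA that ignores the result. The effect measures for mRS, MGS and EQ-5D-5L are therefore not fixed in advance.

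The conflict between the two rules follows from the text alone. Rejection for mRS and MGS follows from their few categories under any plausible shares. The 20% to 78% range depends on the assumed shapes, 138 per arm and a 5% level.

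A reader might infer inflated false-positive rates or a weakened primary analysis, and neither is supported. Recurrence is binary and outside the pre-test, the sample size does not depend on it, and the simulated type I error stays near 5%.

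**What to change.** Delete the normality pre-test. In the same section, name one summary, one effect measure and one method for each secondary outcome, the same at every visit, and rewrite the ANOVA sentence to match:

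- **mRS and MGS:** the distribution by category, with an ordinal (proportional-odds) or rank-based comparison in place of ANOVA.
- **EQ-5D-5L score:** a difference in means with 95% CI from one repeated-measures model adjusted for the baseline value already collected.

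Medians may be added as description. The cost is a few lines in the protocol or analysis plan, with no further data, visits or patients.
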